#### Eligibility Criteria and Recruitment Procedures

The inclusion criteria for this study have been defined with precision to select the most suitable candidates in alignment with the study objectives. We are targeting survivors of stroke, both male and female, aged between 18 and 75 years, who exhibit equinovarus foot secondary to hemiparesis, affecting either the left or right side. A prerequisite for potential participants is their current use of AFOs. Furthermore, the concurrent use of any assistive technologies such as tripods, crutches, or canes is deemed acceptable. Essential criteria include the capacity to provide informed consent and the ability to ambulate, either independently or with the support of the aforementioned devices. Conversely, candidates with concomitant neurological or orthopedic conditions that might confound the study outcomes, those with active dermatological conditions, or those with severe communication impairments potentially hindering consistent participation will be excluded.

The recruitment process will be at the Centro de Medicina de Reabilitação da Região Centro. Attending physicians will review patient profiles to identify individuals meeting the stipulated criteria. Those aligning with our research parameters will be briefed on the study’s aims and subsequently provided with a detailed consent document. Upon granting written consent, these individuals will be enlisted as participants, ensuring a systematic and ethically rigorous approach to data acquisition and feedback.

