#### Clinical Outcomes

In the pursuit of developing an optimized orthotic design system, an array of clinical metrics is implemented to gauge its efficiency, efficacy, and the comfort it bestows on both patients and health care professionals. Ensuring a comfortable experience for the patient during the photography process is paramount, given its pivotal role in orthotic design. This precision not only benefits the patient but also ensures that the system health care professionals navigate is intuitive.

Biomechanical assessments use the Qualisys Miqus M3 system, paired with Bertec force platforms. Patients will wear the Calibrated Anatomical System Technique lower body marker set, which consists of 36 reflective markers, as prescribed by Cappozzo et al [20]. Observations cover 3 walking conditions for each participant: unaided (where possible), with the current orthosis, and with the newly designed orthosis. This methodology provides an in-depth understanding of the orthosis’s efficacy, drawing from 10 walking cycles for each leg, and analyzing both kinematics and kinetics.

The biomechanical data under scrutiny spans temporal-spatial parameters, which capture walking speed, gait cycle duration, step length, step time, time in stance, and time in swing. Kinematic parameters delve into pelvic movements such as anterior tilt, up obliquity, and internal rotation. Hip parameters include flexion, adduction, and internal rotation, while knee parameters assess flexion, varus, and internal rotation. Ankle and foot evaluations note dorsiflexion, inversion, pitch, and internal progression. Kinetic parameters are marked by the internal moments at the hip (extensor and valgus), knee (extensor and valgus), and ankle (plantarflexor and extensor), accompanied by the vertical ground reaction force.

The qualitative patient analysis will also incorporate the QUEST assessment. QUEST focuses on understanding the user’s satisfaction with assistive technology. It evaluates a range of aspects, from device functionality to user confidence. This offers insights into patients’ perceptions and benefits derived from the new orthosis in comparison to conventional models. Incorporating QUEST ensures the orthosis not only meets clinical requirements but also aligns with patient preferences and comfort levels.

Through these comprehensive evaluations, the study aims to offer an enriched perspective on the potential and effectiveness of the innovative orthotic system.

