### Data Analysis

The forthcoming data analysis is designed to provide an in-depth understanding of the impact of personalized orthoses on gait parameters in relation to both preexisting orthosis and barefoot walking. The sample size was estimated at a prespecified power of 90%, while the α value was set at <.05. The primary outcomes will be represented through spatial-temporal data tables and normalized gait graphs, spanning from 0% to 100% of the gait cycle for the left and right legs.

Spatial-temporal parameters will undergo statistical comparisons using paired *t* tests. This will discern any significant differences between walking with the personalized orthosis, the preexisting orthosis, and walking barefoot. Significant distinctions will be recognized based on *P* values, with a threshold set at 95% indicating statistical significance.

Graphical comparisons of kinematic and kinetic data will use the Statistical Parametric Mapping (SPM) method. SPM is tailored for the analysis of 1D biomechanical data series, such as kinematic curves, yielding a nuanced understanding of differences across the entire gait cycle rather than mere isolated time points. The analysis will leverage the *SPM1D* script. By using SPM1D, it becomes feasible to pinpoint regions in the gait cycle where palpable differences between conditions (existing orthosis, personalized orthosis, and barefoot) arise. This rigorous method offers a continuous evaluation over the entire time or space continuum, safeguarding against missing subtle yet clinically pivotal variations.

Simultaneously, the QUEST responses will be statistically analyzed to evaluate patient satisfaction. Scores from the QUEST, which range from 1 (not satisfied) to 5 (very satisfied), will be presented as mean and SD values for each question. A 1-sample *t* test will be used to determine if the mean satisfaction scores significantly differ from a neutral value. Additionally, a Wilcoxon signed rank test may be used to determine differences in satisfaction levels between using the personalized orthosis and the preexisting orthosis. Any statistically significant variations in user satisfaction between the 2 orthoses will provide insight into the preferential use and comfort of the personalized design.

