## Results

The methodology and approach of this research harbor specific expectations concerning its outcomes. We will use the Qualisys Track Manager from Qualisys to capture biomechanical data with unparalleled accuracy. Once gathered, the data will be processed and analyzed rigorously. With the integration of the Project Automation Framework from Qualisys and Visual 3D from C-Motion, the raw biomechanical data will be transformed into actionable insights that promise to inform and refine orthotic design.

One of the primary quantitative expectations is that the orthosis developed through the new system will either match or surpass the performance of the patient’s current orthosis. This benchmark stems from the belief that the integration of state-of-the-art technology and personalized biomechanical data can achieve superior orthotic design. On the qualitative front, using the QUEST assessment, the expectation leans toward higher satisfaction rates with the new orthosis. Since the orthosis is tailored specifically to the patient’s leg, it is anticipated that its unique design will resonate more with patients, ensuring better fit, comfort, and overall user experience. To ensure comprehensive results, feedback from health care professionals and participants will be actively sought throughout the trial phases. This blend of qualitative and quantitative data aims to present a holistic perspective on the impact of the new orthotic design, setting the stage for potential breakthroughs in patient-centered orthotic solutions. In summary, while this research protocol lays out the groundwork and anticipated outcomes, the subsequent study will seek to not just present numbers but to demonstrate the tangible and intangible benefits of a personalized orthotic approach.

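### Limb-specific gait outcomes are laid out by left and right leg although either side may be paretic; pooled that way, braced and unbraced limbs mix and the orthosis effect is diluted

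*Protocol article*

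**What the plan says.** All references are to the protocol article.

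- **Data Analysis**, layout of the primary outcomes: spatial-temporal tables and normalized curves "spanning from 0% to 100% of the gait cycle for the left and right legs".
- **Eligibility Criteria and Recruitment Procedures**, who enters: survivors of stroke with "equinovarus foot secondary to hemiparesis, affecting either the left or right side".
- **Clinical Outcomes**, what is recorded: both limbs, "drawing from 10 walking cycles for each leg, and analyzing both kinematics and kinetics", under three conditions, "unaided (where possible), with the current orthosis, and with the newly designed orthosis".
- **Results**, where the device goes: "Since the orthosis is tailored specifically to the patient’s leg", in the singular.
- **Data Analysis**, tests: "Spatial-temporal parameters will undergo statistical comparisons using paired *t* tests"; for curves, "Graphical comparisons of kinematic and kinetic data will use the Statistical Parametric Mapping (SPM) method". Neither sentence names a limb or a side.

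No section organises an outcome or a test by paretic, braced, affected or contralateral limb.

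**The concern.** The orthosis is worn on the paretic side, and that side differs between participants. Within one participant, a left/right display is harmless, because the braced side is the same under both orthoses. Across participants it is not. A group 'left leg' series contains braced paretic limbs from left-hemiparetic patients and unbraced limbs from right-hemiparetic patients.

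The change from one orthosis to another acts mainly on the braced limb. A pooled mean therefore shrinks toward whatever happens on the other limb, by an amount set by the accidental side mix of the sample. A true difference becomes harder to detect. The Study Design section declares a noninferiority aim for biomechanical outcomes, and there shrinkage toward zero works in the other direction: a new orthosis that performs worse on the braced limb looks closer to the existing one than it is.

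This is more than silence. The article states a limb classification for its primary outcomes, and that classification does not match the treated limb.

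**Working it through.** **No figure to reproduce.** Data Analysis states 90% power and an alpha of .05, but the article gives no sample size, effect size, SD, margin or side split. What follows is an illustration.

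**Inputs**
- From the article: paired t test, 90% power, alpha 0.05.
- Assumed: two-sided test; SD of paired differences = 1; true effect on the braced limb d = 0.5, 0.8 or 1.0; share p of participants braced on the leg analysed; effect on the other limb = c × d.

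**Formulas for the pooled 'leg'**
- Mean difference = p·d + (1 − p)·c·d
- Variance of the difference = 1 + p(1 − p)·[d(1 − c)]²
- Effective standardized effect = mean / √variance, with power from the noncentral t distribution

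**Worked case: d = 0.8, p = 0.5, c = 0**
- Mean = 0.5 × 0.8 = 0.40
- SD = √(1 + 0.25 × 0.64) = √1.16 = 1.077
- Effective effect = 0.40 / 1.077 = 0.371
- By affected limb, 90% power needs n = 19. With the same 19 analysed by anatomical side, power is 34%. Restoring 90% would need n = 79.

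Almost all of the loss comes from the halved mean; the SD rises by less than 8%.

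**50:50 split, no effect on the other limb**

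| d on braced limb | n for 90% power by affected limb | Effective effect by side | Power by side, same n | n for 90% power by side |
|---|---|---|---|---|
| 0.5 | 44 | 0.243 | 35% | 181 |
| 0.8 | 19 | 0.371 | 34% | 79 |
| 1.0 | 13 | 0.447 | 32% | 55 |

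**Sensitivity, same n (range over the three values of d)**

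| Share braced on that side | Effect on other limb | Mean kept | Power |
|---|---|---|---|
| 30% | none | 30% | about 15–16% |
| 50% | none | 50% | 32–35% |
| 70% | none | 70% | 56–60% |
| 50% | one quarter of d | 62.5% | 49–51% |

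Simulation with 40,000 replicates per cell agreed with these powers to within half a percentage point. The 30% and 70% rows can be the two legs of one trial: if 30% are braced on the left, 70% are braced on the right. A compensatory change of opposite sign on the other limb would dilute the mean further.

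**Noninferiority direction.** If the braced limb is worse by d and the other limb is unchanged, the pooled mean at 50:50 is worse by only d/2. Any margin between d/2 and d would be breached by the braced limb but not by the pooled mean.

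**Outcomes not affected.** Walking speed and gait cycle duration belong to the whole gait, not to one limb, so side labelling does not alter them.

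**The case against.** The strongest reply is that the quoted words describe display, not testing. The sentences on the t test and SPM name no side, and the left/right graphs may be individual gait reports, in which nothing is mixed. This is also a condensed article, and a statistical analysis plan that is not shown could relabel limbs before pooling.

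The first part stands and sets the limit of the point. A reader might infer that the article prescribes side-based group tests and that real differences will therefore be missed. The text does not support that: dilution follows only if the group tests use the displayed layout. What remains is that left/right is the only layout given, and it is given for the primary outcomes. An analysis plan that used affected and unaffected limbs would have to depart from it.

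Other parts also stand:
- Not every primary outcome is touched; walking speed and gait cycle duration are exempt.
- Every power figure is assumed. The sample sizes of 44, 19 and 13 are back-calculated from chosen effects and are not this trial's numbers, so a reader should not conclude that the trial has about one third of its intended power.
- A reader might infer that the layout will produce a false noninferiority claim. The article states no margin and specifies difference tests, so no such conclusion can be computed from it. Dilution could mask a worse result, and no more can be said.

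**Conclusion.** The point holds as a conditional one. The only limb layout stated for the primary gait outcomes does not identify the treated limb in a sample whose treated side varies. If group tests and SPM follow it, the effect on limb-specific outcomes is diluted in proportion to the side mix.

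Under the assumptions shown, nominal 90% power falls to roughly one third at an even split. The range is about 15% to 60% across splits of 30% to 70%, and power is about half if the other limb carries a quarter of the effect. The direction does not depend on the chosen values so long as the other limb responds less than the braced one; the size does.

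In a feasibility study, with wording that may describe presentation only, this is a clarification to make before analysis. It does not show that the analysis is already invalid. It is worth making because it needs no new data and removes a later, data-driven choice of limb.

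**What to change.** In Data Analysis, replace the left/right layout with 'for the affected (orthosis) limb and the unaffected limb'. Apply it to:

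- the spatial-temporal tables and group gait graphs;
- the paired tests of limb-specific parameters (step length, step time, stance, swing);
- all SPM comparisons of joint angles, moments and ground reaction force.

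Name the affected limb as primary and report the unaffected limb separately. Align side-dependent pelvic angles (obliquity and rotation) to the affected side before pooling. Walking speed and gait cycle duration need no change, and left/right graphs may stay for individual participants.

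The cost is one side flag per participant in data processing. Both legs are already recorded, so no extra measurement or recruitment is needed.

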**Results:**

Spatial-temporal parameters will be statistically compared using paired *t* tests to determine significant differences between walking with the personalized orthosis, the existing orthosis, and barefoot conditions. Significant differences will be identified based on *P* values, with *P*<.05 indicating statistical significance. The Statistical Parametric Mapping method will be applied to graphically compare kinematic and kinetic data across the entire gait cycle. QUEST responses will undergo statistical analysis to evaluate patient satisfaction, with scores ranging from 1 (not satisfied) to 5 (very satisfied). Satisfaction scores will be presented as mean and SD values. Significant variations in satisfaction levels between the personalized and existing orthosis will be assessed using a Wilcoxon signed rank test. The anticipation is that the AFOs crafted through this innovative system will either match or outperform existing orthoses in use, with higher patient satisfaction rates.

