## Methods

### Study Design

This nonrandomized feasibility study aims to harness advanced scanning technologies and innovative software for the design and refinement of orthotics tailored specifically to the unique anatomical and biomechanical needs of survivors of stroke presenting with equinovarus deformity. Following a noninferiority trial design for biomechanical outcomes and a superiority trial design for qualitative outcomes, our methodology focuses on the development of a novel AFO system. The goal is to ensure its biomechanical performance is at least as effective as off-the-shelf AFOs while also enhancing patient satisfaction. Feedback from patients and clinical observations will serve as the primary indicators of success.

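### The Methods give the P-value threshold for the spatial-temporal t tests as 95%, contradicting the abstract's P<.05; the sample-size alpha is written as an inequality

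*Protocol article*

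**What the plan says.** Three places in the protocol article bear on the significance level.

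- **Methods, Data Analysis, decision rule.** The tests are named first: "Spatial-temporal parameters will undergo statistical comparisons using paired" t tests, covering the personalized orthosis, the preexisting orthosis and barefoot walking. Differences are then recognised from P values, "with a threshold set at 95% indicating statistical significance".
- **Abstract, Results.** For the same paired t tests, the rule is P"<.05 indicating statistical significance".
- **Methods, Data Analysis, sample size.** "The sample size was estimated at a prespecified power of 90" percent, "while the α value was set at <.05". Sidedness is not given.

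Study Design supplies the framework: "Following a noninferiority trial design for biomechanical outcomes and a superiority trial design for qualitative outcomes".

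**The concern.** The Data Analysis sentence is the operative rule for the spatial-temporal parameters, and that section counts their tables among the primary outcomes. The sentence attaches a confidence level to a P value, so it cannot be applied as written, and it disagrees with the abstract.

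The sample-size sentence has a related fault. An inequality describes how a P value is compared with alpha. Alpha itself must be a single number, with a stated side, before 90% power has a definite meaning.

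The wording matters somewhat more here because two kinds of inference are declared. A 95% level belongs naturally to a confidence limit, as used for noninferiority. P<.05 belongs to a test for a difference. A sentence that blends the two does not help the reader see which rule applies to the biomechanical comparison.

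**Working it through.** **1. Do the three statements agree on a level?**

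| Place | As written | Read as a nominal level |
|---|---|---|
| Abstract, Results | P<.05 | .05 |
| Data Analysis, decision rule | P values, threshold 95% | 1 − 0.95 = .05, if 95% is a confidence level |
| Data Analysis, sample size | alpha <.05 | .05, if the inequality is a slip for equality |

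Read this way, the abstract's .05 is reproduced. Taken literally as a P-value cut-off, .95 does not match .05. The article names no other level.

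**2. Does the correction change a computed figure?** No. Changing 95% to P<.05, and <.05 to = .05, leaves the nominal level at .05. The article prints no number of participants, effect size, standard deviation or margin, so the sample size can be neither reproduced nor shown to change.

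**3. What if the original calculation was one-sided?** The article is silent on this, so it is an assumption. For a paired comparison under the normal approximation, n = (z_alpha + z_power)² / d², where d is the standardised paired difference.

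- Two-sided .05 with 90% power: (1.960 + 1.2816)² = 10.51.
- One-sided .05 with 90% power: (1.645 + 1.2816)² = 8.56.

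If n was set from the second line, then d√n = √8.56 = 2.926. Tested at two-sided .05, power is Φ(2.926 − 1.960) = Φ(0.97) ≈ 0.83. The value of d cancels, so the result does not depend on the missing effect size. If the calculation was already two-sided, power stays at 90%.

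**The case against.** The strongest reply is that this is an editorial slip in a condensed article whose own abstract gives the right value. That largely stands. Nobody would run the tests at a cut-off of .95, and the three statements are three phrasings of one 5% level.

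A reader might infer more:

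- **That the trial has no valid significance level, or three competing ones.** The documents do not support this. The abstract fixes P<.05 for these very tests, and the other two statements fit it.
- **That P<.95 would be applied.** Nothing in the article supports that reading, and the abstract rules it out.
- **That alpha <.05 leaves the sample size open to stricter levels.** No stricter level is named anywhere. The difference between 8.56 and 10.51 comes from sidedness, not from the inequality.

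It is also fair to say that declaring noninferiority while describing only tests for differences is a separate mismatch, which correcting the 95% would not cure. Sidedness, margin and sample-size inputs may be in the full protocol or analysis plan, so their absence from the article is not held against it.

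What the reply does not remove is the misstatement. The article prints a wrong threshold in its Methods and contradicts it in its abstract, and no document outside the article can make that sentence right.

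**Conclusion.** The point holds as a minor correction to an operative sentence. The decision rule in Data Analysis confuses a confidence level with a P-value threshold and contradicts the abstract, and alpha in the sample-size sentence should be a fixed value. The evident intention throughout is a nominal 5% level, so no printed figure changes.

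The only numerical consequence is conditional. If the sample size was computed at one-sided .05, power for the two-sided test is about 83%. That figure assumes the normal approximation and the same standardised difference.

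**What to change.** 1. In Data Analysis, replace the 95% threshold by: significant if two-sided P<.05, for the difference and superiority tests. This then matches the abstract.
2. In the sample-size sentence, write alpha = .05 and add the sidedness actually used. If that was one-sided, restate the power for the two-sided test.
3. Because Study Design declares noninferiority for the biomechanical outcomes, add that noninferiority is concluded from the relevant limit of the two-sided 95% confidence interval for the paired difference, compared with the prespecified margin, and not from the P value of a difference test.

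Items 1 and 2 cost a few words, apart from a possible restatement of power (about 83% in the one-sided case). Item 3 is more than wording: it needs the margin, which the article does not print and which should be taken from the full protocol.
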